## **8.10. Support telephone line**

There will be a telephone helpline for the local research team to access advice in case of any technical issues.

## **8.11. Participant reimbursement**

The study will provide the CGM device, insulin pump, smartphone (where required) and related consumables. A study payment will be made to reflect local practice. The amount paid will be specified in the participant information sheet and REC application form. Reasonable travel expenses will be reimbursed. After completing the study, participants will not keep the study devices. They will revert to their usual insulin therapy and glucose monitoring.

## **8.12. Healthcare Professional Interviews (UK only)**

Interviews will be conducted with healthcare professionals (n=20, 2-3 per site) involved in trial recruitment and delivery, recruited from UK-based sites. Interviews will be scheduled near the end of the trial and/or when the healthcare professional stops working on it (e.g., due to changing job), to maximise the wealth of experience of supporting closed-loop system use upon which interviewees can draw. Interviews will be informed by topic guides which will be revised in light of emerging findings, in line with an inductive approach.

## 9. Endpoints

### 9.1. Efficacy endpoints

#### 9.1.1. Primary efficacy endpoint

The primary endpoint is the between group difference in centralised measurement of glycated haemoglobin (HbA1c) at 26 weeks.

#### 9.1.2. Other key endpoints

- Proportion of time spent in the target glucose range (3.9 to 10.0mmol/l)\*
- Mean sensor glucose\*
- Proportion of time spent above target glucose (>10.0mmol/l) \*
- Non-inferiority for time spent below target glucose (<3.9mmol/L) \*

#### 9.1.3. Secondary efficacy endpoints

- Standard deviation and coefficient of variation of glucose\*
- Proportion of time with glucose <3.5mmol/l and <3.0mmol/l\*
- Proportion of time with glucose >13.9 mmol/l, >16.7mmol/l and >20.0mmol/l \*
- Binary metrics for HbA1c (HbA1c <7.0%[53mmol/mol], HbA1c <7.5%[58.5mmol/mol])
- Total daily insulin dose
- Body weight, waist hip ratio and Body Mass Index
- Fasted lipid profile
- Renal function as measured by sodium, potassium, urea, serum creatinine, estimated Glomerular Filtration Rate and urinary albumin creatinine ratio
- Liver function as measured by liver markers (ALT, AST, ALP, γGT, bilirubin and albumin) and FIB4 index

\*Glucose related endpoints based on CGM data over 26 weeks

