## **8.2. Visit 1 - Recruitment visit and screening assessment**

Potential participants will be given a verbal explanation of the study and will have the opportunity to ask any questions. If they agree to proceed with the study, and providing they meet the inclusion/exclusion criteria, participants will give written informed consent to a member of the research team. Those who would prefer to have more time to consider their decision to participate can return and give consent at a later date.

At the screening visit, participant's height, weight, waist hip ratio, blood pressure, demographics, medical and diabetes history, concomitant medications and insulin therapy will be recorded. Participants will have blood tests including HbA1c, fasted lipid profile, renal function and liver function. Urine albumin creatinine ratio (ACR) will be measured. A urine pregnancy test will be performed in all females aged between 18 and 60 years. A masked continuous glucose monitor (CGM) will be applied to assess baseline glycaemic control and participants will be asked to complete questionnaires to assess quality of life and diabetes management.

Participants will then proceed to the run-in period (2-3 weeks) where they will use their usual insulin therapy and wear the masked CGM. For those already using CGM as part of their usual care, they can continue with their usual CGM and also wear the masked study CGM. There will be a minimum of two weeks run-in period for all participants (end of Visit 1 to Visit 2).

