## **8.6. Visit 4 – 3 month visit**

Participants will attend the research centre for Visit 4 approximately three months after Visit 3. Participants will have a blood test for HbA1c, fasted lipid profile, renal function and liver function. Participant's weight, waist hip ratio and BP will be recorded and urine ACR measured. Participants will be asked to complete questionnaires to assess quality of life and diabetes management.

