#### **11.1.2. Venepuncture**

- Venous blood samples for the measurement of HbA1c levels will be taken at baseline, at 3 months and at the final study visit. HbA1c will be measured at a central laboratory using an International Federation of Clinical Chemistry and Laboratory Medicine (IFCC) aligned method. HbA1c testing will follow National Glycohemoglobin Standardization Program (NGSP) standards. Samples will be stored locally until analysis at the central laboratory.
- Venous blood samples for the measurement of fasted lipid profile, renal function (sodium, potassium, urea, serum creatinine, estimated Glomerular Filtration Rate) and liver function (ALT, AST, ALP,  $\gamma$ GT, bilirubin and albumin) will be taken at baseline, at 3 months and at the final study visit and will be analysed locally. Blood samples will be disposed of after analysis.

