#### *Insulin and other endpoints:*

- Total daily insulin dose
- Body weight, waist hip ratio and Body Mass Index
- Blood pressure
- Fasted lipid profile
- Renal function as measured by sodium, potassium, urea, serum creatinine, estimated Glomerular Filtration Rate and urinary albumin creatinine ratio
- Liver function as measured by liver markers (ALT, AST, ALP,  $\gamma\text{GT}$ , bilirubin and albumin) and FIB4 index

Trends in CGM and insulin data collected within intervention arms will be evaluated on a monthly basis and daytime (0600 to 2359) and overnight (0000 to 0559) glucose control will be evaluated separately.

For the pre-specified key endpoints and secondary endpoints, mean  $\pm$  SD or summary statistics appropriate to the distribution will be reported for the primary endpoint over the 26 week period by treatment intervention and tabulated by treatment group. Analysis of secondary endpoints will parallel the primary analysis. A transformation will be applied to all highly skewed secondary endpoints.

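### FIB4 index is a secondary endpoint, but no platelet count is specified at any visit, so the endpoint cannot be calculated from the protocol's data

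*Protocol*

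**What the plan says.** FIB4 appears as an endpoint in three places: the synopsis (Study endpoints), section 9.1.3 and section 13.2. Section 9.1.3 ends its list of liver markers with "bilirubin and albumin) and FIB4 index". In section 13.2 it falls in the subcategory of insulin and other endpoints, for which Benjamini-Hochberg adjusted p-values are planned.

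Section 11.1.2 defines the blood tests. One sample is for HbA1c alone: "Venous blood samples for the measurement of HbA1c levels will be taken at baseline, at 3 months and at the final study visit". The other covers the remaining analytes: "Venous blood samples for the measurement of fasted lipid profile, renal function (sodium, potassium, urea, serum creatinine, estimated Glomerular Filtration Rate) and liver function", the liver part being ALT, AST, ALP, γGT, "bilirubin and albumin) will be taken at baseline, at 3 months and at the final study visit and will be analysed locally". On retention of that second set it says: "Blood samples will be disposed of after analysis".

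The visit descriptions name the same groups and nothing further. Section 8.2 (Visit 1) reads "Participants will have blood tests including HbA1c, fasted lipid profile, renal function and liver function". Section 8.6 (Visit 4) reads "Participants will have a blood test for HbA1c, fasted lipid profile, renal function and liver function", and section 8.7 (Visit 5) has the same list. Tables 1 and 2 in section 8.1 agree.

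**The concern.** FIB-4 is a composite with a fixed formula, and one of its four components is the platelet count. The protocol names no platelet count and no full blood count, so it promises an endpoint for which it does not collect the data.

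This differs from a detail that a protocol may leave to its analysis plan. An analysis plan can write down the formula, units and handling of extremes, but it cannot supply a laboratory value that was never measured. What is at stake is a prespecified secondary endpoint that would have to be reported as not available, or computed only for those participants who happen to have a count on file from routine care. Availability of routine counts could differ by site, so that subset could be a selected one.

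Timing adds to the concern. Section 22 plans first inclusion in September 2024 and the last participant's completion in March 2027, and the latest version in the amendment history is dated 14.10.2025. On that timetable some visits will already have passed without a count, and more will follow until the protocol is changed.

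**Working it through.** The check is a tracing of inputs. The plan gives no figure for this endpoint that could be reproduced.

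**Formula (standard definition, not in the protocol).** FIB-4 = age × AST / (platelets × √ALT).

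**Each input against the protocol:**

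| Input | Source in the protocol | Available? |
|---|---|---|
| Age | Demographics at Visit 1, section 8.2 | Yes |
| AST | Liver function, section 11.1.2 | Yes, three visits |
| ALT | Liver function, section 11.1.2 | Yes, three visits |
| Platelet count | Not in 11.1.2, Tables 1 and 2, sections 8.2, 8.6, 8.7 or the synopsis | No |

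**Internal comparison.** The renal and liver blood analytes in section 11.1.2 match the endpoint list in section 9.1.3 item for item. Urinary albumin creatinine ratio is covered in 11.1.3. Other derived measures are supported: BMI has height and weight (11.1.1), and eGFR is itself in the panel. FIB4 is the one item in the renal and liver lists with no matching measurement.

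**Could it be approximated without platelets?** As an illustration, assume age 60, AST 30 U/L and ALT 30 U/L, and vary platelets over an assumed 150 to 400 × 10⁹/L:

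- 150: 60 × 30 / (150 × √30) = 2.19
- 250: 60 × 30 / (250 × √30) = 1.31
- 400: 60 × 30 / (400 × √30) = 0.82

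With everything else fixed, the index changes by a factor of 400/150 ≈ 2.7. The analytes that are collected do not determine it.

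**Could it be measured later?** The lipid, renal and liver samples are discarded after analysis. The HbA1c sample is held only until central analysis, and no other assay is assigned to it.

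**Size.** With 224 randomised:

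- All three scheduled visits: 224 × 3 = 672 values, the ceiling before dropout.
- A baseline-adjusted 26-week comparison, since section 13.2 says the secondary analyses parallel the primary one: 224 × 2 = 448 values.
- The 26-week outcome alone: 224 values, or about 0.8 × 224 = 179 under the 20% dropout assumed in section 13.11.

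On the panel as specified, none of these can be computed.

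**The case against.** Five points can be made on the other side.

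- **The formula is not in the protocol.** True; the finding rests on the standard definition of a named index. But that definition is what the endpoint's name means, and the formula is not in dispute.
- **The Visit 1 wording is open.** Section 8.2 introduces its blood tests as an inclusive list, and Tables 1 and 2 do the same for the baseline bloods, so a baseline count is not strictly ruled out. This stands as a limit on wording: the exact statement is that no platelet count is specified. It does not rescue the endpoint, because section 11.1.2 sets out the analytes for all three visits without platelets, and the lists for Visits 4 and 5 are closed.
- **Routine care may supply counts.** Participants continue to see their clinical teams, so some values may be obtainable. How many is unknown, and the protocol neither asks for them nor sets a time window. Complete and irrecoverable loss is therefore not certain, but the protocol itself secures no values.
- **The harm is small.** Section 13.2 calls these secondary endpoints exploratory, and six individual liver markers are still measured. A missing p-value does not invalidate the false-discovery-rate adjustment of the others; it means only that the declared family is larger than the one that can be tested. This stands and limits the weight of the point.
- **672 overstates the loss.** It is a ceiling over three visits. The planned 26-week comparison depends on at most 224 outcome values plus their baselines.

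**Conclusion.** The concern holds. The protocol names FIB4 as a secondary endpoint and specifies three of its four inputs. Followed as written, it produces no FIB-4 value at any visit: none of up to 224 at 26 weeks, and none of up to 672 over the three visits. The gap lies in data collection, so an analysis plan cannot close it.

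The conclusion assumes the standard FIB-4 definition and that sites measure what section 11.1.2 lists. If some sites obtain blood counts anyway, the result would be a partial endpoint whose availability the protocol does not control. The effect is confined to one secondary endpoint, labelled exploratory; the primary endpoint and the fixed-sequence key endpoints are unaffected. It should be corrected, and the sooner the better, because each further visit without a count is lost unless routine care happens to supply one.

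**What to change.** Choose one of two changes.

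1. **Keep the endpoint.** Add a platelet count to the local panel in section 11.1.2, to Tables 1 and 2, to sections 8.2, 8.6 and 8.7 and to the matching synopsis entries, at baseline, 3 months and end of study. State whether a dated routine-care count may be used where a visit has already passed, and within what window. State also how participants without a baseline value enter the baseline-adjusted comparison.
2. **Drop the endpoint.** Delete FIB4 from the synopsis, section 9.1.3 and section 13.2, so that the adjusted subcategory holds only endpoints that can be tested.

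The first costs one routine local assay at venepunctures already scheduled, and will leave some missing baselines among those already enrolled. The second has no measurement cost. Both need a protocol amendment, and if it counts as substantial, section 17 requires ethics approval before implementation, here across 15 sites in seven countries. That effort is modest if the change is carried in the next amendment.

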#### 9.1.4. Exploratory endpoints

- Day (06:00 to 23:59) and night (00:00 to 05:59) glucose control
- Monthly trends in glucose control and insulin delivery

## **9.2. Safety evaluation**

Safety evaluation will comprise the number of episodes of severe hypoglycaemia, as well as nature and severity of any other adverse events including SAEs, SADEs and AEs over 26 weeks. All participants including those who withdraw will be included in the safety evaluation.

## **9.3. Utility evaluation**

Utility evaluation is the acceptability and duration of use of the CGM and closed-loop system over the 26 week intervention periods.

## **9.4. Human factors evaluation**

Expectations, attitudes and responses to the closed-loop system will be assessed using validated questionnaires (perceptions of quality of life, burden of diabetes management, and fear of hypoglycaemia) as well as qualitative interviews with selected participants and healthcare professionals supporting closed-loop users (UK sites only).

## **10. Assessment and Reporting of Adverse Events**

### **10.1. Definitions**

#### **10.1.1. Reportable Adverse Events**

A reportable Adverse Event is any untoward medical occurrence that meets criteria for a serious adverse event or any unanticipated medical occurrence in a study participant that is study or device-related. Device deficiencies that could have led to a serious adverse device effect will also be reported (ISO 14155: 8.2.5 and 9.8).

#### **10.1.2. Adverse Events**

An adverse event (AE) is any untoward medical occurrence, unintended disease or injury, or untoward clinical signs (including abnormal laboratory findings) in a participant, users or other persons, who has received an investigational device, whether or not related to the investigational medical device (ISO 14155: 3.2). This definition includes events related to the device under investigation or the comparator or to the study procedures. The following anticipated adverse events will not be recorded:

- Non clinically significant skin reactions as judged by investigator
- Pre-existing medical conditions
- New illnesses or conditions not requiring concomitant medication or medical intervention/procedures
- Non severe hypoglycaemia
- Hyperglycaemia without significant ketonaemia (<3mmol/L)

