#### **6.1.2. Exclusion criteria for all countries**

1. Type 1 diabetes
2. Current use of insulin pump
3. Current use of any closed-loop system
4. Any physical/psychological disease or medication(s) likely to interfere with the conduct of the study and interpretation of the study results, as judged by study clinician
5. Known or suspected allergy against insulin
6. Pregnancy, planned pregnancy, or breast feeding
7. Severe visual impairment
8. Severe hearing impairment
9. Medically documented allergy towards the adhesive (glue) of plasters
10. Serious skin diseases located at places of the body, which potentially are possible to be used for localisation of the glucose sensor
11. Illicit drugs abuse
12. Prescription drugs abuse
13. Alcohol abuse

Potential participants with diabetes related retinal disease will not be excluded from the trial. An individualised risk approach will be used, and we will consider delaying recruiting people undergoing active treatment of proliferative retinopathy / maculopathy until treatment is complete.

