## **8.8. Participant withdrawal criteria**

The following pre-randomisation withdrawal criterion will apply:

1. Participant is unable to demonstrate safe application of insulin therapy as judged by the investigator.

The following pre- and post-randomisation withdrawal criteria will apply:

2. Participant is unable to demonstrate safe use of insulin injections or study insulin pump, CGM and/or closed-loop during post randomisation training period as judged by the investigator.
3. Participants may terminate participation in the study at any time without necessarily giving a reason and without any personal disadvantage
4. Significant protocol violation or non-compliance
5. Recurrent severe hypoglycaemia events related to the use of the closed-loop system
6. Recurrent severe persistent hyperglycaemia events/DKA unrelated to infusion site failure and related to use of the closed-loop system
7. Decision by the investigator or the Sponsor that termination is in the participant's best medical interest
8. Allergic reaction to insulin, or severe reaction to adhesive surface of infusion set or glucose sensor

Participants who are withdrawn for reasons stated in (2) to (8) will be invited to provide a blood sample and complete questionnaires at the end of the planned study intervention.

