## **8.9. Study stopping criteria**

The study may be stopped if three consecutive participants withdraw from the study for safety reasons, or on the advice of the independent Data Safety Monitoring Board (DSMB).

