#### **10.3.6. Retinopathy**

People with type 2 diabetes have a pre-existing risk of developing diabetic retinopathy, and this risk is increased in those with sub-optimal glycaemic control. However, a rapid improvement in blood glucose levels, as may be seen with a closed-loop system, can sometimes also lead to a worsening of diabetic retinopathy in the short term. Participants will be warned of this risk, and advised to regularly attend retinopathy screening, as is part of routine clinical care.

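### The rule that pre-existing conditions are not recorded as adverse events has no exception for worsening, so non-serious worsening of existing retinopathy, a harm the protocol itself names, can go uncounted

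*Protocol*

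**What the plan says.** Section 10.1.2 defines an adverse event broadly and then gives a list introduced by the words "The following anticipated adverse events will not be recorded". It has five entries. One is "Pre-existing medical conditions", with no qualification. Another is "Hyperglycaemia without significant ketonaemia (<3mmol/L" (the protocol closes the bracket there).

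Three other places bear on the first entry:

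- Section 6.1.2: "Potential participants with diabetes related retinal disease will not be excluded from the trial".
- Section 10.3.6: rapid improvement in glucose, as may be seen with closed-loop, "can sometimes also lead to a worsening of diabetic retinopathy in the short term".
- Section 10.3.6 again: participants are warned of this and "advised to regularly attend retinopathy screening, as is part of routine clinical care". The visit schedule (Tables 1 and 2) contains no study eye examination.

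Two places bear on the second entry:

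- Section 8.8, withdrawal criterion 6: "Recurrent severe persistent hyperglycaemia events/DKA unrelated to infusion site failure and related to use of the closed-loop system".
- Section 8.9: the study may be stopped if "three consecutive participants withdraw from the study for safety reasons".

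The counts by arm come from section 13.3, which tabulates adverse events and serious adverse events per participant, severe hypoglycaemia and diabetic ketoacidosis. Sections 10.6 and 19.1 give the DSMB compiled adverse event data at intervals.

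**The concern.** The list is meant to keep expected background events off the forms. Its entry on pre-existing conditions does not separate a condition that is merely present from one that gets worse during the trial. For most comorbidities this would be a small matter. For retinopathy it is not, because the protocol admits people who already have it and names its worsening as a possible consequence of the effect the device is designed to produce.

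At stake is the by-arm safety comparison for a harm the protocol itself foresees. If sites follow the list literally, non-serious worsening leaves no adverse event record, and neither the final tables nor the DSMB's compiled data would show it. There are 15 sites in seven countries, so sites may also read the entry differently.

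A lesser concern is that the recording rules do not match withdrawal criterion 6. Part of that criterion rests on hyperglycaemia events for which no event record is required.

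**Working it through.** No arithmetic applies and the protocol gives no figure to reproduce. The check sets the sections side by side.

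**Retinopathy**

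1. *Can retinopathy be pre-existing?* Yes. Section 6.1.2 does not exclude it; it only says that delaying recruitment will be considered during active treatment of proliferative disease or maculopathy.
2. *Is worsening anticipated?* Yes. It is described in section 10.3.6, and section 10.3 says that risks and anticipated adverse events are used interchangeably there. It therefore falls in the class that the section 10.1.2 list addresses.
3. *Does the list exclude it?* On its wording, it can. The other four entries each carry a limit: clinical significance for skin reactions, need for medication or intervention for new illnesses, severity for hypoglycaemia, a ketone level for hyperglycaemia. The pre-existing entry carries none. Taken literally, a new illness needing medication is recorded, while worsening of an old one needing medication is not.
4. *Does another section bring it back?* Only in part.
   - Section 10.1.4 makes it serious if it causes permanent impairment or needs intervention to prevent it, and section 10.2.4.1 (UK) requires all serious events to be reported, anticipated or not.
   - Section 10.1.1 does not make a non-serious, anticipated event reportable.
   - Section 10.2.2 says that all adverse events will be recorded but does not mention the exclusions, so the two sections are in tension.
   - Section 8.5 has contacts record changes in other medical conditions and medication, but does not say that these become adverse events.
   - Section 10.3.5 calls for an adverse event form for severe skin reactions to the sensor; section 10.3.6 has no matching sentence.
5. *What is left out?* Non-serious worsening of retinopathy that was present at baseline.
6. *Which arm could it favour?* Section 10.3.6 ties the risk to rapid improvement, as may be seen with closed-loop. In the earlier 8-week crossover study in section 3.4.3, HbA1c was 57 against 72 mmol/mol, a difference of 72 − 57 = 15 mmol/mol in favour of closed-loop. If improvement here is similarly uneven between arms, missing cases would fall more in the closed-loop arm.

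**Hyperglycaemia and criterion 6**

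1. Criterion 6 has two limbs, severe persistent hyperglycaemia and DKA. It requires recurrence, a relation to closed-loop use and no relation to infusion site failure.
2. The DKA limb is covered, because section 13.3 counts DKA events and participants.
3. For the other limb, section 10.1.2 requires no event record when ketones are below 3 mmol/L, unless the event is serious. Section 10.1.6 also leaves infusion set occlusion or leakage below that ketone level off the device deficiency record. Neither form need hold the event or the infusion-site attribution that the criterion uses.
4. Hypoglycaemia is handled consistently: only non-severe episodes are excluded, severe ones get a form (section 10.2.3), and criterion 5 refers to severe events.

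**The case against.** The strongest reply on retinopathy is that the entry most naturally means the baseline condition itself. Worsening is an untoward medical occurrence and so meets the definition of an adverse event; nothing says outright that worsening is excluded. That reading is reasonable, and many sites may adopt it. But the protocol does not state it, and the neighbouring entries show that limits were written in where they were wanted. It is also fair to say that serious worsening is reported, that adverse events are tabulated descriptively, and that the primary and key endpoints are untouched. All of that stands and narrows the point.

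On hyperglycaemia the reply is stronger. A reader might infer that hyperglycaemia is not ascertained at all, that recurrence cannot be followed, or that the omission flatters the device. The protocol does not support any of these. CGM, pump and closed-loop data are uploaded (sections 11.1.4 and 11.1.5). Time above 10.0 mmol/l is a key endpoint, and time above 13.9, 16.7 and 20.0 mmol/l are secondary endpoints (sections 9.1.2 and 9.1.3). Device use is reviewed at scheduled contacts. Sections 7.5 and 10.4 expect less hyperglycaemia on closed-loop, so there is no basis for a bias towards the device on this harm. The DSMB's remit in section 19.1 also covers effectiveness endpoints. What survives is narrower: glucose summaries define no event and assign no cause, and the protocol does not link them to criterion 6.

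A reader might also want a count of missed retinopathy events. Any such count would rest wholly on an assumed rate.

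**Conclusion.** The point holds for retinopathy. On the literal wording of section 10.1.2, worsening of pre-existing retinopathy that meets no seriousness criterion need not be recorded, and would be absent from the by-arm safety tables and the DSMB's compiled adverse event data. The omission could favour the closed-loop arm. This rests on two assumptions: that at least some sites apply the entry as written, and that improvement is faster on closed-loop, as section 10.3.6 allows. Its size cannot be stated from the document.

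For hyperglycaemia only an inconsistency remains. Sections 10.1.2 and 10.1.6 require no event record or infusion-site attribution for non-serious events with ketones below 3 mmol/L, while criterion 6 in section 8.8 uses both. The efficacy analysis is not affected by either part.

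**What to change.** - In section 10.1.2, limit the entry to pre-existing medical conditions that have not worsened since baseline, and make section 10.2.2 refer to the list so that the two agree.
- In section 13.3, add reported worsening of retinopathy to the events tabulated by arm, and include it in the DSMB's compiled data.
- Reconcile sections 10.1.2 and 10.1.6 with criterion 6 in section 8.8, so that any hyperglycaemia event counted towards that criterion is documented with its attribution, whatever the ketone level. The criterion and the thresholds need not change.

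The cost is a wording amendment, CRF guidance and some extra adverse event forms. The contacts in section 8.5 already ask about changes in medical conditions, so no new visit is needed. The change improves recording, not detection: eye examinations remain in routine care, so a by-arm count will reflect what that care finds and should be reported with that limit stated.
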